**Method and analysis:**

An explanatory sequential mixed methods design will be used. In the quantitative phase, a randomized controlled trial and RM-ANOVA will compare night wakings in infants whose parents receive Play2Sleep versus standard public health nursing information. Sixty English-speaking families (mothers and fathers) of full-term, healthy, singleton, 5-month-old infants who perceive that their infant has sleep disturbances will be recruited. The primary outcome measure will be change in the number of night wakings reported by parents. The qualitative component will use thematic analysis of family interviews to describe parental perceptions and experiences of infant sleep. Mixed methods integration will use qualitative findings to explain quantitative results.

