### Sample Size

The effect size for the sample size calculation for the quantitative phase was estimated from research that examined brief sleep interventions with the number of night wakings as the primary outcome. A study of a brief internet intervention for families of young children up to age 3 years that provided a customized sleep program, with and without a standardized bedtime routine, found relatively large effect sizes (partial eta squared) of 0.442 and 0.441, respectively (49). In a narrower age group of infants 6–12 months, Hall and colleagues (50) found an effect size (Cohen’s *d*) of 0.64 for an intervention that included a 2-h teaching session and telephone support for parents. An *a priori* analysis was conducted in G*Power for repeated measures ANOVA, between factors (51). This calculation determined that a total sample size of 60 mother–father–infant triads (30 families in each group) would detect an effect size of 0.32 with a power of 0.80 at a 0.05 level of significance (Figure 2), which is below the effect size of the aforementioned studies (49, 50). Recruitment will be ongoing until complete data are collected from 60 families. Based on previous studies (37, 39), attrition is estimated to be very low (less than 5%) after the initial home visit. Figure 3 shows the proposed Consolidated Standards of Reporting Trials flow diagram.

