### Measures

The primary infant sleep outcome will be the frequency of night wakings, as measured by the expanded version of the Brief Infant Sleep Questionnaire [BISQ (48, 53)]. The BISQ is not a psychometric scale, but a screening questionnaire that can be used in clinical practice and research. The expanded version of the BISQ is a multi-dimensional 32-item screening tool (53) developed from the well-established original 13-item tool (48, 54). The original and expanded BISQ both include items covering the domains of sleep ecology, infant sleep patterns, and caregiver perception of infant sleep. However, using the expanded version of the BISQ addresses limitations of previous studies where unspecific and incomplete information on daytime sleep, longest consolidated period of sleep, and sleep ecology, all of which may influence the families’ subjective perception of the presence of sleep problems (53). Given that the BISQ is a screening questionnaire and not a scale, Sadeh (48) did not provide a Cronbach’s α for the BISQ. Secondary outcomes for this study will include (1) nocturnal wakefulness, (2) sleep latency (the length of time it takes parents to put the infant to sleep in the evening, with responses captured as “less than 5 min,” “5–15 min,” “16–30 min,” “31–60 min,” and “more than 1”), (3) the longest consolidated sleep episode, and (4) parental perception of problematic infant sleep; these secondary outcomes will also be measured using the expanded BISQ. The expanded BISQ will be administered as part of a complete study online questionnaire package that includes questionnaires measuring covariates, in the 5–7 days before each of the baseline and outcome home visits. Outcome and covariate measures are presented in Tables 2 and 3. Demographic information, including (1) parental age, education, ethnicity, and income; and (2) infant age, birth order, and feeding type will be collected. At baseline and outcome, parents will be asked to describe the techniques, strategies, and resources that they use to promote infant sleep, which will be explored further during the qualitative interviews.

**Table 2 T2:** Measure for primary (frequency of night wakings) and secondary (nocturnal wakefulness, sleep latency, longest consolidated sleep episode, and parental perception of problematic infant sleep) outcomes.

Measure	Description

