### Stepwise Procedure

#### Data Collection and Management

This community-based study will use both an online format and in-person home visits to collect baseline and outcome data (for a schedule of assessment, see Table 4) from both mothers and fathers separately. Families will be assigned a unique study identification number, which will be used to link mothers and fathers of the same family.

**Table 4 T4:** Play2sleep study schedule of enrollment, interventions, and assessments.

Study period						
	Enrollment	Baseline	Randomization	Initial visit	Outcome visit	Family interview
Time point	*−t*2	*−t*1	0	*T*1	*T*2	*T*3

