**Assessments**						
*Expanded BISQ*		X			X	
*PCITS*				X	X	
*EPDS*		X			X	
*IBQ-R very short form*		X			X	
*MCISQ*		X			X	
*DAS-4*		X			X	
*PSOC*		X			X	
*Interview*						X

*BISQ, Brief Infant Sleep Questionnaire; PCITS, Parent–Child Interaction Teaching Scale; EPDS, Edinburgh Postnatal Depression Scale; IBQ-R, Infant Behavior Questionnaire—Revised; MCISQ, Maternal Cognitions about Infant Sleep Questionnaire; DAS-4, Brief version of the Dyadic Adjustment Scale; PSOC, Parental Sense of Competence*.

Online study questionnaires, hosted on Qualtrics, will be used to collect the majority of data on outcomes and covariates at baseline, when the infant is aged 5 months, and at outcome, when the infant is aged 7 months. Qualtrics is a recognized and secure electronic survey system that houses data on secure Canadian servers. Parents (mothers and fathers) in both groups will each complete baseline questionnaires in the 7 days prior to the initial home visit. A link to the baseline questionnaires will be emailed to parents 5–7 days before the home visit, and an email reminder encouraging parents to complete the questionnaires prior to the home visit will be sent if necessary.

The first home visit will occur when the infant is 5 months old (±2 weeks), at a time that is convenient to the family. [name] and colleagues (38) have demonstrated 5 months of age is a feasible time-point to begin a video self-modeled intervention. Scheduling the home visit when the infant is 5 months of age will allow sufficient time between referral to the study at the 4-month well-child clinic visit and scheduling of the first home visit. Scheduling the home visits within a 2-week window of 5 months provides a realistic timeframe to schedule visits based on availability of both parents, as well as being able to re-schedule visits if there are unanticipated events (i.e., infant illness). This narrow window minimizes maturation bias due to the rapid developmental changes that occur in infants at this age.

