An automated randomization service (77) will generate the randomization sequence to allocate families to either the experimental or comparison group. Allocation concealment will be achieved because the randomization code will not be requested until the family enrolls in the study and parents complete the baseline questionnaire. After participants have completed the baseline questionnaire and immediately before the initial home visit, the home visitor will submit an online form requesting treatment allocation. A copy of the allocation will be emailed to the home visitor and stored in the study’s online Sealed Envelope Ltd. account.

At the start of the first home visit, participants will affirm their verbal consent (provided during the eligibility screening phone call) by providing written consent. After establishing initial rapport with the parents, the home visitor will ask each parent (mother and father) to teach their infant a unique age-appropriate play task, which is video-recorded by the home visitor to be coded later using the PCITS coding scheme (34). As per the PCITS manual, the video-taped structured teaching and play sequence lasts no longer than 10 min, typically spanning a 3- to 5-min timeframe (34). The order of the video-recordings will alternate between the mother and father to prevent ordering bias. Following the video-recorded structured play session, the home visitor will deliver either the Play2Sleep or comparison intervention. At the conclusion of the home visit, the home visitor will offer to schedule the outcome home visit.

The outcome home visit will occur when the infant is aged 7 months (±2 weeks). Seven months was selected because parents need time to practice and solidify new interaction patterns to translate into measurable effects on infant sleep patterns. Parents (mothers and fathers) in both groups will each complete outcome questionnaires in the 7 days prior to the second (outcome) home visit. During the outcome home visit, parents in both the experimental and comparison groups will again engage their infant in a different play task that is video-recorded for later coding. All families will be offered a listing of local infant sleep-related resources and services. Once data collection is completed, data will be downloaded, backed-up, and deleted from the Qualtrics account.

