## Anticipated Results

### Phase 1 Quantitative Analysis

Quantitative data will be analyzed using IBM SPSS Statistics 24.0 software. Data will be examined for frequency and patterns of missing data. If less than 20% of the data are missing, and if missing at random or completely at random, missing values will be imputed using multiple imputation (80). Descriptive statistics (means, SDs, frequencies, and percentages) will be used to describe the sample, and correlations between variables will be examined to identify potential covariates. Using the “intent to treat” principle, a RM-ANOVA will be used to detect differences between groups over time in mother and father reports of infant sleep patterns that are measured as continuous variables (night wakings, nocturnal wakefulness, and longest period of consolidated nighttime sleep). To control for Type I error that may result from multiple hypothesis testing, we will apply a Bonferroni correction during the analyses. Ordinal level infant sleep variables (sleep latency and parental perception of problematic sleep) will be analyzed using a Wilcoxon signed-rank test. If there are statistically significant differences between groups on the primary outcome, sub-analyses will identify which covariates have significant effects. Parent–child interactions scores for both mothers and fathers will be compared to normed scores available from the NCAST database.

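### Both parents' night-waking reports enter the primary RM-ANOVA, with no rule that yields one family-level primary test

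*Protocol article*

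**What the plan says.** The Abstract defines the primary endpoint without resolving who reports it: "The primary outcome measure will be change in the number of night wakings reported by parents". Measures adds the instrument but no reporter: "The primary infant sleep outcome will be the frequency of night wakings, as measured by the expanded version of the Brief Infant Sleep Questionnaire".

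Data Collection and Management makes clear that there are two reporters. Data are gathered "from both mothers and fathers separately". At baseline, "Parents (mothers and fathers) in both groups will each complete baseline questionnaires in the 7 days prior to the initial home visit"; at follow-up, "Parents (mothers and fathers) in both groups will each complete outcome questionnaires in the 7 days prior to the second (outcome) home visit". A family identifier is assigned, "which will be used to link mothers and fathers of the same family", but no stated model uses it.

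Phase 1 Quantitative Analysis then says that RM-ANOVA will look for "differences between groups over time in mother and father reports of infant sleep patterns that are measured as continuous variables". The next sentence announces a Bonferroni correction for multiple testing, without naming the tests it covers. Covariate sub-analyses follow only if the primary outcome differs significantly between groups.

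Sample Size uses G*Power's repeated-measures ANOVA, between factors, and arrives at "a total sample size of 60 mother–father–infant triads (30 families in each group"), for an effect size of 0.32, power 0.80 and a significance level of 0.05. Phase 2 families are chosen by how much the infant's night wakings changed.

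**The concern.** The infant has one sleep pattern, the family is the randomised unit, and the trial is sized in families. The analysis nevertheless receives two versions of the primary outcome, and nothing says how they become one answer.

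The plain reading is one RM-ANOVA for the mother's reports and one for the father's. That gives two primary p-values. If they disagree, the article does not say whether the trial is positive or whether the covariate sub-analyses are triggered. If neither test is corrected, false positives exceed 5%. If both are corrected, the power calculation no longer matches the test. Phase 2 selection also presupposes a single change per family that is not defined; that has no inferential consequence, but the same definition would settle it.

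**Working it through.** **Inputs from the article.** Total N = 60 families, 1:1; effect size 0.32, read as Cohen's f; power 0.80; alpha 0.05, undivided; two reporters per infant at baseline and at outcome.

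**Inputs assumed.** The number of measurements (m = 2) and their correlation (ρ = 0.5) in the power calculation are not stated. Nor is r, the correlation between the mother's and father's values for night wakings. For a group-by-time test the relevant r is that of the two parents' changes. I use 0.5 to 0.9, with 0.3 as a check. The only mother–father correlations in the article are for other constructs (Table 3): 0.28 to 0.61 for temperament and 0.65 to 0.72 for cognitions about infant sleep.

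**Step 1: reproduce the sample size.** For RM-ANOVA, between factors, the noncentrality is λ = f²·N·m / (1 + (m − 1)ρ), with 1 and N − 2 degrees of freedom.
- λ = 0.32² × 60 × 2 / 1.5 = 8.192, with df 1 and 58.
- Power at 0.05 is 0.804, and 60 is the smallest even N that reaches 0.80.

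The stated figure is reproduced for one test at 0.05 with two measurements. This does not prove that one value per family was intended: m = 4 (two parents, two times) with ρ = 0.7 gives 0.791, which is also close.

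**Step 2: two separate tests, uncorrected.** P(at least one false positive) = 1 − P(|Z₁| < 1.96 and |Z₂| < 1.96), with (Z₁, Z₂) bivariate normal with correlation r.

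| r | At least one false positive |
|---|---|
| 0.3 | 9.5% |
| 0.5 | 9.1% |
| 0.7 | 8.4% |
| 0.9 | 7.0% |

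The limit for independent tests is 1 − 0.95² = 9.75%. A simulation of 40,000 null trials with 30 families per arm agrees: 9.2% at r = 0.5 and 7.1% at r = 0.9. In the same simulation both tests rejected in 0.9% and 3.0% of trials. So the two reporters gave conflicting answers in about 9.2 − 0.9 = 8.3% and 7.1 − 3.0 = 4.1% of trials with no effect.

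**Step 3: two separate tests, Bonferroni at 0.025 each.** Familywise error is held (simulated 4.7% at r = 0.5, 3.7% at r = 0.9). With λ = 8.192 unchanged, power per test falls from 0.804 to 0.712. The detectable f rises from 0.319 to 0.352, and 74 families would be needed for 0.80 per test. The chance that at least one of the two tests rejects is higher than 0.712 and depends on r, but the article does not state an either-reporter rule.

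**Step 4: one family-level value.** Testing the mean of the two reports once at 0.05 gave simulated type I error of 4.8% to 5.3% across the correlations tried. If the two reports have equal variance, the SD of the mean relative to a single report is √((1 + r)/2): √0.75 = 0.87 at r = 0.5 and √0.95 = 0.97 at r = 0.9. Nothing is lost in precision, and alpha stays whole.

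**The case against.** Three points on the other side have weight.

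First, RM-ANOVA can take family as the subject, with parent and time both within-family. That yields a single group-by-time test and accounts for the correlation between parents. The family identifier makes it possible, and the sample size counts triads. Only a condensed article is at hand, and the factor structure may be given in a fuller document. This stands in part: it rules out saying that the analysis must be invalid. It does not remove the point, because the article itself fixes the test, the data entering it, the error control and the sample size, and these do not fit together without a rule that it does not give.

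Second, a Bonferroni correction is announced. If it covers both reporters, error is controlled. This also stands, but the cost then moves to power, which was calculated at the full 0.05.

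Third, r is assumed. That is true, but the uncorrected error stays above 5% throughout the range shown.

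A reader might go further and infer that the plan pools 120 parent records as if independent, with type I error of about 11% to 16%. The article does not support that. It never mentions 120 units, and it counts families or triads in Sample Size and again in Trial Status. Equally, it does not follow that the primary is either tested twice or analysed on non-independent data, since the parent-as-factor model is a valid third course.

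**Conclusion.** The point holds as a defect in how the primary analysis is fixed: two reports of one endpoint, with no primary reporter, combining rule or parent factor, and a Bonferroni correction of unstated scope beside a sample size at an undivided 0.05.

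If the parents are tested separately, the price is either about 7% to 9% familywise error (uncorrected, r from 0.9 to 0.5) or power of about 0.71 per test in place of 0.80 (Bonferroni over two tests, f = 0.32, m = 2, ρ = 0.5). The power figure carries the article's own between-factors calculation over to 0.025; it is not a separate estimate of power for a group-by-time contrast. Inflated type I error is a possible result of the wording, not an established one. The change should be made, because the wording determines what counts as a positive trial.

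**What to change.** Before analysis, state one family-level primary test at 0.05:

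- **Primary value:** the mean of the mother's and father's night wakings at each time, with family as the unit. With complete data, one RM-ANOVA with family as subject, parent and time as within-family factors and a single group-by-time test is equivalent.
- **Missing parent report:** use the multiple imputation already planned, under its stated conditions. Substituting the single available report would depart from that plan and mix values of different variance.
- **Sensitivity analyses:** mother-only and father-only results, not counted as primary tests.
- **Multiplicity:** state that Bonferroni applies to the secondary outcomes.
- **Consistency:** use the same family value to trigger the covariate sub-analyses and to select Phase 2 families.

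The cost is analysis wording. No new data are needed, and the target of 60 complete families stays. At submission 54 triads were enrolled and no interim analysis was planned, so there was room to settle this before analysis. The small downside is that averaging hides differences between parents in awareness of wakings; the two sensitivity analyses show them.

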## Materials and Equipment

### Study Design

This study will employ a mixed methods, explanatory sequential design to evaluate the Play2Sleep intervention, with priority given to the quantitative phase (Figure 1). Phase 1 is a single center, prospective, randomized, controlled, parallel group, two arm, superiority trial with a 1:1 allocation ratio (ClinicalTrials.gov, identifier NCT02742155). Baseline data collection and intervention will occur when the infant is 5 months of age (±2 weeks), with outcomes measured when the infant is 7 months of age (±2 weeks). During Phase 2, interviews will be conducted with a subset of participating families (mothers and fathers together) about their perceptions and experiences related to their infant’s sleep. The interviews will occur after the outcome home visit takes place, and analyzed using thematic analysis. Phase 3, the integration phase, will focus on explaining the quantitative results from Phase 1 using the qualitative findings from Phase 2.

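### The Bonferroni correction does not exempt the primary outcome and is not reconciled with the unadjusted 0.05 behind the sample size; if it covers the primary, power falls below the stated 0.80

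*Protocol article*

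**What the plan says.** The Measures section names one primary outcome: "The primary infant sleep outcome will be the frequency of night wakings", taken from the expanded BISQ. It names four secondary outcomes from the same questionnaire: nocturnal wakefulness, sleep latency, longest consolidated sleep episode, and parental perception of problematic sleep.

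The Sample Size section describes a G*Power calculation for "repeated measures ANOVA, between factors". It concludes that 60 families ("30 families in each group") "would detect an effect size of 0.32 with a power of 0.80 at a 0.05 level of significance". It mentions no adjustment for multiple tests.

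The Phase 1 Quantitative Analysis section assigns the RM-ANOVA to three continuous outcomes in mother and father reports, with night wakings listed first and two of the secondary outcomes after it. The next sentence reads, in its operative part, "we will apply a Bonferroni correction during the analyses". The two ordinal outcomes, both secondary, appear only after that sentence. The section does not say which tests form the corrected family, how many there are, or whether the primary is inside or outside it.

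**The concern.** A trial with one primary outcome, tested once, needs no correction of that test for its secondary outcomes. Here the correction is announced immediately after a list that includes the primary, so a reader following the text would most naturally apply it there too. The significance threshold for night wakings would then be 0.05 divided by some unstated number, and the 0.80 power computed at 0.05 would no longer describe the test.

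Two things are at stake. One is power: the trial may be less able to detect its target effect than the article claims. The other is the decision rule. With between 2 and 10 tests in the family, the threshold lies between 0.025 and 0.005, against 0.05 if the primary is exempt. A primary p-value between 0.005 and 0.05 could be called positive or negative depending on a choice made after the result is known. The covariate sub-analyses also depend on this threshold, because the same section makes them conditional on a significant primary result.

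**Working it through.** **Inputs from the protocol article**
- Effect size 0.32, read as Cohen's f, the G*Power ANOVA metric (Sample Size; the metric is not named there).
- N = 60, 30 per group (Sample Size); 1:1 allocation (Study Design).
- Power 0.80 at alpha 0.05 (Sample Size).
- Test: repeated-measures ANOVA, between factors (Sample Size).

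**Inputs assumed**
- Number of measurements m = 2 and correlation rho = 0.5. The article gives neither.

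**Reproducing the stated figure**

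For the between-factors test, the noncentrality parameter is

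lambda = f² × N × m / (1 + (m − 1) × rho) = 0.1024 × 60 × 2 / 1.5 = 8.192,

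with 1 and N − 2 = 58 degrees of freedom. Power is the probability that a noncentral F with these parameters exceeds the critical value of the central F at the chosen alpha. At alpha 0.05 this gives 0.804, and 60 is the smallest even total N that reaches 0.80. The stated figure therefore reproduces at the unadjusted alpha.

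**Power if the correction covers the primary**

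The same lambda and degrees of freedom apply; only alpha changes, to 0.05 / k for k tests.

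| Tests k | Possible family | Alpha | Power at N = 60 | Total N for 0.80 |
|---|---|---|---|---|
| 1 | Primary exempt | 0.05 | 0.804 | 60 |
| 2 | Night wakings, mother and father | 0.025 | 0.712 | 74 |
| 3 | Three continuous outcomes | 0.0167 | 0.654 | 80 |
| 5 | All five outcomes | 0.01 | 0.581 | 90 |
| 6 | Three continuous outcomes, two parents | 0.0083 | 0.555 | 94 |
| 10 | All five outcomes, two parents | 0.005 | 0.483 | 102 |

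The families with 5 and 10 tests include the two ordinal outcomes, which are analysed by a different test. They enter only by setting the divisor; the power shown is always that of the night-wakings test.

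**Sensitivity to the assumed correlation**

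With rho = 0.3, power goes from 0.856 uncorrected to 0.727 with 3 tests. With rho = 0.7, it goes from 0.753 to 0.590. The level shifts, but the loss from a three-test correction remains about 13 to 16 percentage points (0.856 − 0.727 = 0.129; 0.753 − 0.590 = 0.163).

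**The case against.** The strongest objection is that the article never says that the primary is corrected. That reading comes from the order of the sentences. If the correction is meant for the secondary outcomes only, the sample size and the analysis section are both true and power stays at 0.80. This stands. A reader might infer that the two sections contradict each other, or that the trial has definitely lost its 80% power; the text supports neither, because the scope is left open.

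A related objection is that the exact family for a multiplicity correction is often left to a statistical analysis plan, and none is shown. That would answer a complaint about missing detail. It does not fully answer this one, because the article itself fixes both a correction and an alpha and leaves them unreconciled.

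A reader might also infer that correcting the primary could serve no purpose at all. That goes too far. The analysis uses mother and father reports, and the article does not say whether they yield one primary test or two. If each were tested separately at 0.05, with either able to establish the effect, the error rate could reach 1 − 0.95² = 0.0975 were the tests independent, and less if they are correlated. A correction across two such tests would have a real function. So it is not enough to say that night wakings is tested at 0.05; the handling of the two reporters must be fixed as well.

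Finally, the power figures belong to the between-factors test of the sample size, whereas the analysis section looks for group differences over time. They show what the correction does to the stated calculation and should not be read as the power of the analysis that will be run.

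**Conclusion.** The point holds as an unreconciled pair of statements with a conditional cost. The correction is announced without exempting the primary, and the sample size uses the full 0.05. On the natural reading that the primary is covered, power under the stated design is about 0.71 to 0.48 for 2 to 10 tests, not 0.80. If the primary is exempt, nothing is lost. The size rests on reading 0.32 as Cohen's f, on the assumed two measurements with correlation 0.5, and on a number of tests that the article does not give. It merits correction because, as worded, the rule undercuts the stated power of the trial's single primary hypothesis and leaves its significance threshold open.

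**What to change.** Before unblinding, add one or two sentences to the analysis section stating that:

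- night wakings is the single primary test, at two-sided 0.05, without correction;
- it is one test because either one parent's report is named as primary or both reports enter one joint mother–father model;
- Bonferroni, or Holm, applies only to the four secondary outcomes, with the number of tests in that family given.

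The alpha in the Sample Size section then holds as stated. If the sponsor prefers to keep a correction on the primary, for example across separate mother and father tests, the power should be restated at the adjusted alpha (about 0.71 for two tests under the assumptions above).

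The clarification needs no new data and no change in sample size. Re-sizing would be harder: the Trial Status note reports 54 families enrolled of an expected 61, while restoring 0.80 at a corrected alpha would take a total of 74 to 102 complete families.

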The proposed nursing theory described by [name] and [name] (41) forms the theoretical underpinnings of this study. Informed by Bronfenbrenner’s ecological theory (42, 43) and Barnard’s Model of parent–child interactions (44), [name] and [name] guide nurses to consider parental knowledge and beliefs about infant sleep with the family’s synchrony, not only relating to sleep but also the family’s ability to engage in effective parent–infant interactions. As such, nurses are encouraged to enhance parental knowledge related to infant sleep, as well as the underlying foundational familial interactions that support parental ability to apply knowledge relating to infant sleep during daily and foundational parent–infant interactions. Play2Sleep is an intervention that uses personalized feedback of structured parent–infant play sessions. This approach could help address broader parenting difficulties that may underlie infant sleep disturbances by enhancing parental ability to identify and respond appropriately to their infant’s specific sleep-related and social cues. This study extends previous self-modeled, video-recorded interaction guidance interventions and aims to evaluate Play2Sleep to improve infant sleep. This protocol was prepared in accordance with the SPIRIT guidelines (45), as well as the TIDieR checklist and guide (46) for reporting of interventions.

The overarching mixed methods research aim is to understand how parental perceptions of family experiences, processes, and contexts related to infant sleep explain the effectiveness of Play2Sleep. The objective of the quantitative phase is to compare the effect on infant sleep of one dose of Play2Sleep delivered during home visits with mothers and fathers of 5-month-old infants with sleep disturbances against standard infant sleep education only. The primary hypothesis is that Play2Sleep will decrease the number of night wakings at the age of 7 months. The objective of the qualitative phase is to describe parental perceptions of family experiences, processes, and contexts related to Play2Sleep and infant sleep.

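### The Wilcoxon signed-rank test named for the two ordinal secondary outcomes is a paired test and cannot compare the randomised arms

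*Protocol article*

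**What the plan says.** Study Design describes Phase 1 as a "prospective, randomized, controlled, parallel group, two arm, superiority trial with a 1:1 allocation ratio". The quantitative objective at the end of the Introduction is to compare Play2Sleep "against standard infant sleep education only".

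Measures lists four secondary outcomes, all from the expanded BISQ: nocturnal wakefulness, sleep latency, longest consolidated sleep episode, and the parents' view of infant sleep as a problem. Latency is recorded in five ordered time bands.

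Phase 1 Quantitative Analysis splits the outcomes by scale. For the continuous ones (night wakings, wakefulness, longest episode), "a RM-ANOVA will be used to detect differences between groups over time in mother and father reports of infant sleep patterns". For the other two, "Ordinal level infant sleep variables (sleep latency and parental perception of problematic sleep) will be analyzed using a Wilcoxon signed-rank test". A Bonferroni correction is also promised, with no divisor given. Nothing else in the article tests the ordinal outcomes between arms.

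**The concern.** The signed-rank test works on differences within pairs. No matching of families across arms is described, so the available pairs are the 5- and 7-month answers of one family, or mother and father in one family. Neither is a treatment contrast. Applied to change over time, the test gives a p-value for each arm or one for all families together. The only way to reach a statement about Play2Sleep is then to note that one arm reached significance and the other did not, which is not a test of the difference.

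The article itself gives reasons to expect improvement in both arms:

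- Limitations says that the motivation of enrolling families may inflate improvement in both groups.
- Participants admits only infants over poor-sleep thresholds whose parents perceive a disturbance, so some regression to the mean is likely (an inference; the article does not say it).
- Comparison Group describes an individualised sleep-education discussion of about 30 minutes, which the Play2Sleep arm also receives.

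If this shared change is read as efficacy, two of the four secondary outcomes could be reported as favourable with no arm difference behind them.

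**Working it through.** **Inputs from the article.** Two independent arms of 30 families (Sample Size); two measurement times, 5 and 7 months (Study Design); five ordered categories for sleep latency (Measures).

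**The plan's own figure.** The only power figure concerns the primary analysis: N = 60, effect size f = 0.32, alpha 0.05, power 0.80. For the between factor of a repeated-measures ANOVA with m = 2 times, and a correlation of 0.5 that the article does not state:

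λ = f² × N × m / (1 + (m − 1)ρ) = 0.1024 × 60 × 2 / 1.5 = 8.19, on 1 and 58 degrees of freedom.

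This gives power 0.804, so the stated 0.80 is reproduced (0.856 at ρ = 0.3; 0.753 at ρ = 0.7). The figure does not bear on the ordinal outcomes, but it confirms 30 per arm as the size to use below.

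**Simulation.** The following are assumptions: a latent normal score with 5-to-7-month correlation 0.5, cut at −1.2, −0.4, 0.4 and 1.2 into five categories; the same improvement in both arms, so no treatment effect; two-sided 0.05; 3,000 trials per row (Monte Carlo standard error at most √(0.25/3000) = 0.9 percentage points). Entries are the percentage of trials.

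| Improvement in both arms | Signed-rank, Play2Sleep arm | Signed-rank, all 60 families | One arm significant, the other not | Rank-sum between arms, change | Rank-sum between arms, 7 months |
|---|---|---|---|---|---|
| none | 5.8 | 5.0 | 10.2 | 5.0 | 5.4 |
| 0.3 SD | 30.3 | 54.8 | 42.5 | 4.6 | 4.8 |
| 0.5 SD | 67.6 | 94.3 | 44.7 | 5.0 | 5.2 |
| 0.8 SD | 96.9 | 100 | 6.3 | 4.2 | 4.7 |

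**Check on discordance.** The arms are independent with the same rejection probability p, so discordance is 2p(1 − p). At 0.5 SD this is 2 × 0.68 × 0.32 = 0.44. The half that favours Play2Sleep is 0.68 × 0.32 = 0.22.

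**With a real arm effect.** With improvements of 0.8 SD under Play2Sleep and 0.3 SD in the comparison arm, the pooled signed-rank test rejects in 96.7% of trials. It rejects in 94.3% when both arms improve by 0.5 SD and there is no arm effect, so it hardly distinguishes the two situations. The rank-sum test moves from about 5% to 36.4% (change scores) or 42.6% (7-month scores).

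**The case against.** - **Possible slip.** The authors may have meant the Wilcoxon rank-sum test. That is plausible, but the text names the other test, and the same sentence needs correcting either way.
- **Inference not stated.** The article does not say that the test is run per arm, or that a significant result in one arm only would count as evidence. This is fair: the before/after reading follows from the test and the two-visit schedule. The text does establish that the named test has no arm comparison and that no other test supplies one.
- **Overstated size.** The discordance of about 44% counts both directions, and only about 22% would favour Play2Sleep. The simulation also ignores the Bonferroni correction. At an assumed level of 0.01 (five outcomes), significance in the Play2Sleep arm at 0.5 SD falls from 68% to about 38%. Both points stand. A stricter level lowers the rate but does not turn a time contrast into an arm contrast.
- **Unsupported inputs.** Shift sizes, cut-points and correlation are not in the article, and five categories are documented only for latency. This is true. The percentages depend on these choices, but the absence of an arm term does not.
- **Limited reach.** The primary outcome and the other two secondary outcomes go to a between-group analysis, and the planned primary paper centres on night wakings. This limits the consequence to the two ordinal outcomes.
- **Detail left to an analysis plan.** This does not apply, because the article fixes a specific test that does not fit the design.

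**Conclusion.** The concern holds. As written, sleep latency and the parents' perception of a sleep problem get no test of Play2Sleep against the comparison arm. If the signed-rank result were read as efficacy, the chance of a spurious finding in the Play2Sleep arm would be about 30% to 97% for a shared improvement of 0.3 to 0.8 SD at the unadjusted 0.05 level. A between-arm test stays at 4% to 5%. These percentages rest on the assumed correlation, cut-points and shifts; the structural conclusion does not. The primary analysis and N = 60 are not affected.

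**What to change.** Replace the sentence on ordinal variables with a between-arm analysis: proportional-odds regression of the 7-month category on arm, adjusted for the 5-month category, reporting the odds ratio with a 95% confidence interval. A rank-sum (Mann-Whitney) test between arms, on change or 7-month scores, is an acceptable simpler choice; it does not itself give an odds ratio.

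Both parents report, so analyse mother and father reports separately, or use a model that allows for two responses per family. Do not enter them as independent observations. State the Bonferroni divisor so that it covers these tests. Any within-arm signed-rank result should be labelled descriptive.

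The cost is one rewritten sentence, with the same data and software and nothing further asked of families. With 54 triads enrolled at manuscript submission, the correction should be dated and recorded before any unblinded analysis. A valid test of these outcomes will have modest power: in the simulated case of a 0.5 SD difference between arms, the rank-sum test rejected in about 36% to 43% of trials. A null result should be reported with that in mind.
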